## Abstract

**Background:**

This RCT with two parallel arms will evaluate the efficacy of an internet-delivered transdiagnostic cognitive behavioural therapy (iCBT) intervention for the treatment of clinical depression and/or anxiety in early stage cancer survivors.

**Methods/design:**

Early stage cancer survivors will be recruited via the research arm of a not-for-profit clinical research unit and randomised to an intervention (iCBT) group or a ‘treatment as usual’ (TAU) control group. The minimum sample size for each group is 45 people (assuming effect size > 0.6, power of 80%, and alpha at .05), but 10% more will be recruited to account for attrition. A solitary or cumulative diagnosis(es) of Major Depressive Episode (current), Generalised Anxiety Disorder, Illness Anxiety Disorder, Panic Disorder, Agoraphobia, and/or Adjustment disorder will be determined using modules from the Anxiety Disorders Interview Schedule for DSM-5. Depression and anxiety levels with be measured via the total score of the Hospital Anxiety and Depression scale (HADS-T), the primary outcome measure. Secondary measures will include the Kessler 10 to measure general distress, the Fear of Cancer Recurrence Inventory (FCRI) to measure the specific fear of cancer recurrence and the Functional Assessment of Cancer Therapy, General Version 4 (FACT-G) for self-report of physical, social, emotional and functional well-being. iCBT participants will complete the measures before lessons 1 and 5, at post-treatment and at 3-month follow-up. The TAU group will complete similar measures at weeks 1, 8 and 16 of the waiting period. Program efficacy will be determined using intent-to-treat mixed models. Maintenance of gains will be assessed at 3-month follow-up. Mediation analyses using PROCESS will be used to examine the association between change in depressive and anxious symptoms over time and changes in FCRI and FACT-G QOL in separate analysis.

**Discussion:**

This is the first RCT looking at iCBT specifically for clinical depression and/or anxiety in a cancer population. Findings will help to direct the role of iCBT in streamlined psycho-social care pathways.

**Trial registration:**

Australian New Zealand Clinical Trials Registry: ACTRN12616000231448, registered 19^th^ February 2016 (www.anzctr.org.au). This trial protocol is in compliance with the Standard Protocol Items: Recommendations for Interventional Trials (SPIRIT) guidelines.

## Background

Emotional health problems are significantly higher in cancer survivors (defined as per the National Cancer Institute (NCI) definition, from the time of cancer diagnosis to the end of life) than in the general population. In a recent study, across the different types of cancer, 19% of patients had clinical levels of anxiety, and 12.9% having clinical levels of depression. In addition, other patients had subclinical levels of anxious (22.6%) and depressive (16.5%) symptoms [1]. Many cancer survivors suffer long-term emotional distress with symptoms of anxiety and depression often persisting for years following completion of cancer treatment [2]. There is a need for sustainable delivery of effective interventions for depression and anxiety in routine cancer care.

## CBT for the treatment of depression and anxiety in cancer

Fortunately there are clinically effective interventions available for the treatment of clinical depression and anxiety disorders in the cancer setting. A 2012 meta-analysis [3] concluded that Cognitive Behavioural Therapy (CBT) is an effective treatment for depression in cancer care while earlier studies found evidence for CBT in treating anxiety [4]. Additionally CBT in cancer care represents good value for money [5]. The barriers to accessing the clinically and cost-effective evidence based treatment of face-to-face CBT for depression and/or anxiety in the psycho-social context include: under-recognition of the problem by the patients, under-recognition of the need for screening and treatment of emotional health problems within teams and the lack of appropriately trained mental health professionals in many communities to provide evidence based care to cancer patients [6]. Leykin et al. [7] noted that too few cancer patients and survivors receive evidence-based interventions for psychological difficulties and that “*internet interventions have the potential to fill an important gap in quality cancer care by augmenting limited available mental health services*”. Furthermore, internet interventions overcome privacy and stigma concerns, allow access to therapy at a time and place convenient to the patient, including those living in rural and remote communities, and are reliable, cost-effective and reproducible [8–10].

## Online CBT for emotional health problems comorbid with physical illness

Online cognitive-behavioural interventions (iCBT) have been demonstrated to be effective for mild to severe anxiety and depression in the general population [11] and the overall effect-size is comparable to face-to-face CBT [12]. International interest is increasing in harnessing internet delivered interventions, such as iCBT, to tackle emotional health symptoms in patients with comorbid physical health conditions. Trials are underway to evaluate iCBT in treating comorbid emotional health symptoms in Cardiology [13, 14], HIV [15] and Diabetes [16].

There are numerous online programs, including some iCBT interventions, to assist cancer patients. A 2015 literature analysis identified *five* social support groups, *seven* online systems integrating information and *four* online therapies for psycho-social/physical symptoms [17]. Some programs are beginning to show results. In early stage cancer care, the ‘Finding My Way’ trial [18] provided preliminary support for the efficacy of an online intervention that teaches participants skills to adjust and cope after cancer diagnosis. Two further recent small studies have focused on the emotional health of cancer survivors. A recent Dutch RCT evaluated the ‘Cancer Aftercare Guide’, a self-management e-Health intervention [19, 20] which showed clinically relevant decreases of depression and fatigue in cancer survivors. An Australian feasibility study specifically for testicular cancer (eTC) survivors showed preliminary results in lowering depressive symptoms in a small group of survivors [21]. There are now larger trials underway looking at iCBT for severe fatigue in breast cancer survivors [22].

However, no intervention has been evaluated in a randomised controlled trial for a clinical depressive and/or anxiety disorder. A pilot program looking an CBT principles in a cancer survivor population with varying depressive symptoms [23] “*suggests that properly designed web-based interventions may be effective for reducing depressive symptoms among cancer patients*” and a Canadian feasibility open trial using a transdiagnostic iCBT intervention, in a group of 18 participants, showed the potential of using iCBT to decrease depressive and anxious symptoms in cancer survivors [24].

## ADAPT and development of iCanADAPT

The development of iCBT tailored to the cancer context and its integration into clinical care pathways is desirable at a system wide level to allow the integration of physical and emotional treatment. Clinical pathways provide evidence-based recommendations to guide best practice and consistent care for specific patient concerns in homogeneous patient groups. Clinical pathways are desirable at a system wide level to allow increased access to an appropriate level of interventions according to the severity of the patients’ symptoms [25]. ‘ADAPT’, or the ‘Anxiety and depression pathway program’, is a large multi-centred clustered implementation RCT funded by Cancer Institute NSW in 2015. ADAPT will evaluate different strategies of integrating and/or improving psycho-social care pathways in cancer care. One of the strategies included in the ADAPT program is the potential future use of iCBT as a treatment intervention. The ‘iCanADAPT Early’ iCBT program was developed as part of ADAPT to specifically address the needs of early stage cancer survivors, with a co-morbid clinical depressive and/or anxiety disorder.

The Clinical Research Unit for Anxiety and Depression (CRUfAD), UNSW at St Vincent’s Hospital, Sydney, has developed a number of iCBT programs for anxiety and depressive disorders including a transdiagnostic mixed anxiety and depressive disorder program for the general population [26]. CRUfAD modified this proven intervention and further specific cancer content was included. The further content was influenced by current evidence-based cancer-specific face to face CBT and a number of recently developed interventions in heterogeneous cancer patients (Finding my way [27], eTC [21]), Conquer Fear [28]). ‘iCanADAPT Early’ was iteratively reviewed by an expert panel comprising psycho-oncologists, psychiatrists, and consumers and revised accordingly. The final iCBT program is clinician supervised and delivered over a sixteen- week time period. The course is broken into eight lessons and tailored to the cancer context. The CBT skills incorporated facilitate the processing of cognitive and affective aspects of the cancer experiences and include stress management, problem solving, and other practical skills to manage symptoms.

Funded by the NSW Institute of Psychiatry, CRUfAD will conduct an RCT of the ‘iCanADAPT Early’ program, comparing the iCBT intervention to treatment as usual for early stage cancer survivors who meet criteria for a comorbid diagnosis of anxiety and/ or depression.

## Aims of ‘iCanADAPT Early’ study

To examine the efficacy of a clinician-guided iCBT intervention in early stage cancer survivors experiencing anxiety and/or depression symptoms.To determine any concurrent changes in general distress, fear of cancer recurrence, and/or physical, social, emotional and functional status.To capture the feasibility of this iCBT treatment in terms of acceptability to patients.

## Hypotheses

The hypotheses are that, in a patient population characterised by comorbid early stage cancer survivorship AND a clinical depression and/or anxiety disorder:iCBT plus treatment as usual will produce clinically relevant decreases in depressive and anxious symptoms as shown by a decrease in the total Hospital and Anxiety Depression Scale (HADS-T) score (primary outcome measure) compared to a control group receiving treatment as usual.iCBT plus treatment as usual will produce clinically relevant decreases in general distress (Kessler 10), fear of cancer recurrence (Fear of Cancer Recurrence Inventory (FCRI)) and physical, social, emotional and functional status (as measured by the Functional Assessment of Cancer Therapy-General Version scale (FACT-G QOL)).iCBT plus treatment as usual will be perceived by patients to be credible (Credibility/Expectancy Questionnaire(CEQ)), and to be likely to produce positive impacts.

The RCT was approved by the St. Vincent’s Hospital National Human Research Ethics Committees (reference: HREC/15/SVH/432).

## Methods/design

### Study design

This is a parallel group, randomised controlled trial comparing ‘Treatment as usual’ (TAU) plus up to 8 lessons of internet delivered CBT with clinician guidance’ (iCBT) against ‘Treatment as usual’ (TAU).

### Study setting

CRUfAD (Clinical Research Unit for Anxiety and Depression) is a non-profit joint initiative of St. Vincent’s Hospital, Sydney and the University of New South Wales, School of Psychiatry in Australia. CRUfAD specialises in the development, evaluation, and dissemination of evidence-based CBT programs via the internet. This RCT will be conducted within the Virtual Clinic, CRUfAD’s clinical research arm (www.virtualclinic.org.au). The mode of internet recruitment and delivery enables potential participants from all Australian states to apply for enrolment in the current trial.

### Recruitment

Participants will be recruited through flyers, internet social media advertising, cancer support groups and cancer research email listings. Applicants will first complete online screening questionaries about depressive and anxious symptoms and their demographic details will be collected. Inclusion criteria to proceed to the phone interview are as follows; resident of Australia; ≥ 18 years of age, a total score of ≥ 6 on the Hospital Anxiety and Depression scale (HADS-T) and a self-report of early stage cancer or cancer survivorship. This HADS-T cut-off was chosen as it will allow identification of 95% of cases [29, 30]. Applicants will also be asked a number of questions related to the exclusion criteria (see below) and will not proceed to phone interview if they endorse them. Applicants also complete the Alcohol Use Disorders Identification Test Consumption (AUDIT-C) questions but are not excluded on the basis of the results at this stage [31, 32]. See Fig. 1 for a participant flow chart.

**Fig. 1 Fig1:**
[figure not shown]
Participant Flow Chart

### Inclusion/exclusion criteria for participation in the trial

All telephone interviews will be conducted by appropriately trained clinical staff. A psychiatry doctor will undertake the interview if one or more of the following are present: elevated HADS-T; any concerns of risk (elevated passive death wish/suicidality scores); high scores on AUDIT-C).

The inclusion criteria will be confirmed during the interview, namely: early stage cancer survivorship; access to a computer with internet and printer access; Australian residency; fluency in written and spoken English; willingness to provide name, phone number and address; and provision of name and contact details of their local general practitioner. The person will also be invited to identify their treating cancer centre. Upon confirmation of the above, the clinician will undertake the relevant modules from the Anxiety Disorders Interview Schedule for DSM-5. [33] for Major Depressive Episode (current) (MDD), Generalised Anxiety Disorder (GAD), Illness Anxiety Disorder (IAD), Panic Disorder (PD), Agoraphobia (Ag), and/or Adjustment disorder (Adj). The SCID Adjustment module will only be undertaken if the applicant has not met criteria for any of the preceding disorders.

*Cancer related exclusion* criteria will include any reported metastases, currently being an in-patient, being within the first 6 weeks of their cancer diagnosis, having a primary brain cancer (due to potential cognitive changes), a poor physical health status with an exclusion of an ECOG (Eastern Cooperative Oncology Group) performance status of greater than 2.

*Mental health exclusion* criteria will include currently receiving (i)CBT, or undertaking iCBT in the last year, a current or past history of schizophrenia or bipolar disorder, currently taking antipsychotic medications, frequent suicidality (indicated by a score of ≥ 2 to item 9 Beck Depression Inventory-II (BDI-II), or any concerns of active addiction on telephone interview.

At the time of telephone interview, any excluded applicants will receive information on alternative services and will be encouraged to discuss their symptoms with their physician.

Applicants who satisfy all inclusion criteria will complete an electronic informed consent prior to enrolling in the trial. Information from the diagnostic interview will be used for research purposes only for those participants who provide informed consent. All participants will be informed in writing that they may withdraw from the study (i.e. choose to cease program enrolment or choose for their data to be excluded from the RCT) at any time without jeopardising their relationship with St. Vincent’s Hospital or the University of New South Wales. Further, those participants randomised to the treatment as usual group will be informed that should they commence a CBT intervention or new psychotropic medication outside of the trial, their data will be omitted from the RCT.

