### Trial procedure

Figure 1: Participant Flow Chart details the time line for participants in the study. Once randomised, participants will be allocated to either the iCBT arm or the TAU arm. Over the sixteen week period, both groups undertake the same set of measures three times, the start, mid-point and end of the intervention. In the iCBT group, these times will vary according to when the participant undertakes the specific lesson; whereas for the TAU group, the questionnaires are according to specific times (i.e. weeks since commencement of group). Administration time points for measures are contained in Table 1. Baseline records of psychotropic medications and whether they are accessing psychological support will be captured for participants in both groups. Participants will be asked to inform the research team if any of their current interventions change.

**Table 1 Tab1:** Administration time points for questionnaires used in the RCT

Measure	Pre-treatment^a^	Before each lesson^b^	Mid –treatment^c^	Post-treatment^d^	3-month follow-up^b^
HADS-T	♦		♦	♦	♦
K-10	♦	♦	♦	♦	♦
PHQ9-Q9	♦		♦	♦	♦
BDI-II Item 9	♦		♦	♦	♦
FCRI	♦		♦	♦	♦
FACT-G	♦		♦	♦	♦
CEQ	♦			♦	
ADIS	♦				♦

*HADS-T* Hospital Anxiety and Depression Scale,Total score, *K-10* Kessler-10 Psychological Distress Scale, *PHQ9-Q9* Patient Health Questionnaire 9-itme scale, Question 9, *BDI-II Item 9* Beck Depression Inventory-II, Item 9, *FCRI* Fear of Cancer Recurrence Inventory, *FACT-G* Functional Assessment of Cancer Therapy – General, *CEQ* Credibility and Expectancy/Satisfaction Questionnaire, *ADIS* Anxiety Disorders Interview Schedule for DSM-5

^a^iCBT group pre Lesson 1; TAU group at week 1 (Baseline)

^b^iCBT group only

^c^iCBT group pre Lesson 5; TAU group at week 8

^d^ iCBT group post Lesson 8; TAU group at week 16 (End)

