### Measures

#### Primary outcome measure

### Hospital anxiety and depression scale, total score (HADS-T)

The primary endpoint is anxiety and depression severity at post treatment as measured by the Hospital Anxiety and Depression Scale Total score (HADS-T) [35]. The HADS was developed as an outcome measure to assess anxiety and depression that avoids reliance on the measurement of somatic symptoms (e.g., fatigue, or insomnia) that may be experienced by people with cancer as part of the presenting illness. HADS-T is a fourteen item self-report questionnaire divided into two sub-scales, HADS-D, depression subscale and HADS-A, an anxiety subscale. The HADS-T is the total HADS score and is the combined score of the depressive and anxiety sub-scales. High scores indicate greater morbidity. This validated measure is widely used in clinical settings and has been validated in cancer patients [29].

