### Statistical methods

There is no prior published research outlining effectiveness of iCBT for treatment of a clinical depression or anxiety disorder in a cancer setting. In order to calculate sample size, data was taken from published randomised controlled trial of a transdiagnostic iCBT program [26]. Assuming the effect size of >0.6, and taking power at 80% with alpha set at 0.05%, sample size is calculated to be 44 per group. This is to detect a 0.6 effect size for the iCBT group to improve more than the treatment as usual group. Recruitment of 50 per group will be undertaken to account for attrition.

All analyses will be conducted at conclusion of the trial period, i.e. when all participants in the treatment group have completed the iCBT program. All analyses will be implemented in SPSS. Consideration will be given to the stratification into ‘active treatment’ and ‘post-treatment’.

Significance testing of group differences regarding demographic data and pre-treatment measurements will be conducted using analysis of variance (ANOVA) and *χ*2 where the variables consist of nominal (or categorical) data. Intent-to-treat (ITT) mixed models using restricted maximum likelihood (REML) estimation will be used to account for missing data due to participant drop-out. Mixed models do not assume that the last measurement is stable (the last observation carried forward assumption) [48, 49]. REML models are appropriate for RCTs with multiple time points and pre-to post-only designs [50]. The assumption that data are missing at random (MAR) will be evaluated using binary logistic regression to predict drop-out (0 = no drop-out, 1 = drop-out) and by comparing these two groups on baseline measures. Significant effects will be followed up with pairwise contrasts comparing mean pre-treatment to mean post-treatment scores. Mediation analyses will be used to examine the association between change in depression and anxiety symptoms over treatment and change in each of FCRI and FACT-G in separate analyses. Tests of the indirect effects (mediation) will be conducted using PROCESS [51].

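### Ceasing the online program counts as leaving the study, so an iCBT participant who stops lessons has no scheduled post-treatment HADS-T

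*Protocol article*

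**What the plan says.** The consent paragraph (Inclusion/exclusion criteria for participation in the trial) gives participants the following written information: "they may withdraw from the study (i.e. choose to cease program enrolment or choose for their data to be excluded from the RCT". It adds that this may be done "at any time without jeopardising their relationship with St. Vincent’s Hospital or the University of New South Wales". Two acts are listed as forms of withdrawing from the study: ceasing the program, and asking for one's data to be left out.

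Study design describes the experimental treatment as usual care plus "up to 8 lessons of internet delivered CBT with clinician guidance". Trial procedure says of the assessments: "In the iCBT group, these times will vary according to when the participant undertakes the specific lesson". The Table 1 footnotes place the mid-treatment measures before Lesson 5 for iCBT and at week 8 for TAU. They place the post-treatment measures thus: "iCBT group post Lesson 8; TAU group at week 16 (End".

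On the outcome, the HADS-T section states: "The primary endpoint is anxiety and depression severity at post treatment". Statistical methods states: "Intent-to-treat (ITT) mixed models using restricted maximum likelihood (REML) estimation will be used to account for missing data due to participant drop-out". That section examines missing at random by a logistic regression for drop-out, coded as one yes/no variable, and by comparing drop-outs with the rest on baseline measures.

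**The concern.** Stopping treatment and leaving the trial are different events, and an intention-to-treat analysis depends on keeping them apart. Here the first is worded as a case of the second. The lesson-linked schedule adds to the problem, because a participant who never reaches the end of Lesson 8 never meets the trigger for the primary assessment. Nothing in the article provides for stopping the lessons while continuing to answer questionnaires.

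The effect falls mainly on one arm. During the 16 weeks only the iCBT group has lessons to cease; the TAU group is waiting and is assessed by the calendar. A maximum of eight lessons implies that fewer is an allowed course, so the outcomes of people who stop early are part of the treatment effect the trial sets out to estimate. If those who stop tend to have benefited less, their missing post-treatment scores would flatter iCBT on HADS-T, and likewise on the secondary scales measured at the same visits. Outcomes that were never collected cannot be recovered by a later analysis plan.

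**Working it through.** **1. The plan's own figure.** Inputs from Statistical methods and the abstract: standardised effect 0.6, power 80%, 1:1 allocation, alpha 0.05 (the abstract's value; two-sided assumed).
- Normal approximation: n = 2 × (1.960 + 0.842)² / 0.6² = 43.6, rounded up to 44 per group.
- Two-sample t-test: 44.6, rounded up to 45 per group.
- Recruiting 50 per group allows for 1 − 44/50 = 12% or 1 − 45/50 = 10% attrition.

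The figures reproduce. The point does not depend on them, except that 0.6 gives a scale for any bias.

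**2. What is scheduled for a participant who stops lessons.**

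| Event | iCBT, stops before Lesson 5 | iCBT, stops between Lessons 5 and 8 | TAU |
|---|---|---|---|
| Pre-treatment HADS-T | yes | yes | week 1 |
| Mid-treatment HADS-T | trigger not reached | yes | week 8 |
| Post-treatment HADS-T (primary) | trigger not reached | trigger not reached | week 16 |

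The 3-month follow-up does not fill the gap: Table 1 gives it to the iCBT group only, and it falls after the primary endpoint.

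**3. What the mixed model can do.** It uses the retained scores, so a late stopper contributes two HADS-T values and an early stopper one. The missing post-treatment value is in effect predicted from those scores and from the course of participants who continued. That is valid if, given the observed scores, stoppers would have fared like continuers. Predicting drop-out from observed variables and comparing baselines can show that drop-out is related to what was seen. Neither can show that it is unrelated to what was not seen.

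**4. Illustration of bias.** The documents give no stopping rate and no outcome for stoppers, so both inputs are assumptions. Let p be the share of the iCBT arm that stops and d the amount by which their true post-treatment HADS-T is worse than the model predicts. Bias in the iCBT mean = p × d.
- p = 0.20, d = 0.3 SD: 0.06 SD, and 0.06/0.6 = 10% of the planned effect.
- p = 0.40, d = 0.5 SD: 0.20 SD, and 0.20/0.6 = 33% of the planned effect.

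**5. A second view of the same assumption.** Suppose completers gain 0.6 and stoppers gain e. The effect in all randomised participants is 0.6(1 − p) + e × p.

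| Share stopping | e = 0 | e = 0.3 |
|---|---|---|
| 20% | 0.48 | 0.54 |
| 40% | 0.36 | 0.48 |

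An analysis resting on completers' post-treatment scores would tend towards 0.6 unless the earlier scores explain who stops.

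**6. Power, secondary.** With 50 randomised per arm, effect 0.6 and a two-sided t-test at 0.05, power is 84.4% with no loss. With loss in the iCBT arm only it is 79.9% at 20% (40 versus 50) and 72.8% at 40% (30 versus 50). These figures ignore what the mixed model gains from earlier scores.

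**The case against.** The strongest reply is that the consent sentence grants a right and is not a follow-up procedure. The article nowhere says outright that questionnaires end when lessons end. It condenses a fuller protocol, and the consent form and flow chart are not shown. This stands in part: the end of data collection is inferred from the withdrawal wording together with the lesson-linked schedule. But the article does state the definition and does fix the assessment triggers, and the two together leave the stopper without a scheduled primary outcome.

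A reader might infer that stoppers' earlier scores are deleted. The text does not support this. The two acts are joined by an *or*, so ceasing the program does not in itself remove data, and a model meant to handle drop-out presupposes that drop-outs' earlier scores are kept. A reader might also treat data exclusion on request as a fault of the iCBT arm. It is open to participants in both arms, and honouring such a request is not an error.

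Nor do the documents establish the direction of bias. They do not say why people stop; some may stop because they feel better. Clinicians also contact participants who take an unexplained break from logging in, which may reduce stopping.

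Finally, it can be said that the lesson-linked timing is the real cause. The two are distinct: calendar-timed questionnaires alone would not be sent to someone already classed as withdrawn. The rule that TAU participants are told "should they commence a CBT intervention or new psychotropic medication outside of the trial, their data will be omitted from the RCT" is a separate departure from intention to treat, in the other arm, and is not counted here.

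**Conclusion.** The point holds, limited to program cessation. The article classes ceasing the program as study withdrawal and schedules the iCBT primary assessment only after Lesson 8. An iCBT participant who stops lessons therefore has no scheduled post-treatment HADS-T, while TAU participants are measured at week 16 regardless. This is at odds with the stated intention-to-treat aim. The mixed model softens the problem through the retained earlier scores, but fully covers it only under an assumption that the planned checks cannot confirm.

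Bias in favour of iCBT is plausible but not demonstrated, and its size is unknown. The range of 0.06-0.20 SD rests wholly on an assumed 20-40% stopping and an assumed shortfall of 0.3-0.5 SD, with every stopper unmeasured. It shows what could be at stake and is not an estimate for this trial. The analysis is threatened rather than invalidated, and the change is worth making because it is cheap and protects the primary comparison.

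**What to change.** Amend the consent paragraph, and the participant information to match, to say that:
- ceasing the lessons is not withdrawal from the study; the participant stays in the trial and is still sent the remaining questionnaires, at weeks 8 and 16 as for TAU, unless they decline;
- data already collected stay in the intention-to-treat analysis unless the participant explicitly asks for removal.

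Report by arm the numbers who stopped lessons only, who declined further questionnaires, and who asked for their data to be removed. The right to removal on request is unchanged. If the full protocol already keeps people who stop lessons in follow-up, the article's wording should be reconciled with it.

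The cost is a small amendment to the consent wording and some further questionnaires for people who have stopped, which they may refuse. The trial already sends questionnaires by calendar week to the TAU group, so no new form of data collection is needed.

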### Trial design and blinding

The trial is a stratified randomised controlled superiority trial with parallel arms using a 1:1 allocation ratio. It is stratified according to ‘active treatment’ and ‘post treatment’. The ‘active treatment’ group are those who are at least six weeks from their initial cancer diagnosis, and are currently undertaking major cancer treatments such as chemotherapy or radiotherapy. The ‘post treatment’ group are those who have completed their primary treatment for cancer [34] with no upper timeframe. Experimenters and Participants will be aware of their group allocation but as all measures are self-report blinded assessors will not be required.

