### Treatment as usual (TAU) group

Participants allocated to the TAU group may access their local general practitioner, community or cancer centre (mental) health services during the course of their waiting period.

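### Omitting TAU participants who start outside CBT or new psychotropic medication conflicts with the declared intention-to-treat analysis and can bias the primary HADS-T comparison in either direction

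*Protocol article*

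**What the plan says.** In the Protocol article, the consent paragraph under Inclusion/exclusion criteria for participation in the trial sets out a warning addressed to the TAU arm: "should they commence a CBT intervention or new psychotropic medication outside of the trial, their data will be omitted from the RCT". No corresponding statement is made for iCBT participants.

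The Abstract says "Program efficacy will be determined using intent-to-treat mixed models". Statistical methods repeats this: "Intent-to-treat (ITT) mixed models using restricted maximum likelihood (REML) estimation will be used to account for missing data due to participant drop-out". The primary endpoint is HADS-T at post-treatment.

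The section on the TAU group says that its members "may access their local general practitioner, community or cancer centre (mental) health services during the course of their waiting period". Trial procedure adds, after describing both groups: "Participants will be asked to inform the research team if any of their current interventions change". Trial design and blinding states: "Experimenters and Participants will be aware of their group allocation".

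**The concern.** The omission sentence removes randomised people because of something that happens after randomisation. That is not an intention-to-treat analysis, and the article gives no analysis that keeps them.

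Everyone enrolled has a diagnosed depressive, anxiety or adjustment disorder, and the TAU period lasts 16 weeks, so some starts of CBT or medication are foreseeable. Starting plausibly depends on symptoms and plausibly changes them, and HADS-T measures those symptoms. Those omitted are then unlikely to be a random subset of the arm.

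At stake is what the primary contrast estimates. The hypothesis compares iCBT plus TAU with TAU. Under the rule, the control group becomes TAU participants who did not start CBT or new medication, which is narrower than the comparator described in the TAU section. The planned mixed model does not help. REML under missing at random uses the observed scores of people kept in the dataset to deal with missed assessments; someone omitted altogether contributes nothing.

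**Working it through.** **Inputs from the article.** Effect size 0.6, power 80%, 1:1 allocation; 44 per group (Statistical methods) or 45 (Abstract); 50 per group recruited; 10% attrition (Abstract). Alpha is .05 in the Abstract and printed as 0.05% in Statistical methods. An alpha of 0.0005 would need 104 per group, so 0.05 is used here.

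**Inputs not given (assumptions).** The share of TAU omitted, *f*, taken as 10% to 30%. The mean post-treatment HADS-T of starters minus that of non-starters within TAU, *g*, in SD units, taken as -1 to +1.

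**1. The plan's own figure.** n = 2(1.960 + 0.842)²/0.6² = 43.6, so 44 per group. The t-test version gives 44.6, so 45. Then 45/(1 - 0.10) = 50. The sample size reproduces and is not in question.

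**2. Bias formula.** Let the effect be mean TAU HADS-T minus mean iCBT HADS-T, so that positive favours iCBT. If non-starters have mean m, the TAU mean as randomised is m + *fg*. After omission it is m. Bias = m - (m + *fg*) = -*fg*.

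| *f* | size of bias, gap 0.5 SD | size of bias, gap 1 SD |
|---|---|---|
| 10% | 0.05 | 0.10 |
| 20% | 0.10 | 0.20 |
| 30% | 0.15 | 0.30 |

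If starters end worse (*g* > 0) the effect shrinks; if they end better (*g* < 0) it is inflated. At *f* = 20%, a true 0.6 would be estimated as 0.4 to 0.8 over *g* = +1 to -1.

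**3. What could produce the gap, at *f* = 20%.**
- Starters otherwise typical, gaining 0.6 SD from outside care: *g* = -0.6, bias = +0.12 SD.
- Starters are the top 20% on a latent propensity that correlates 0.5 with HADS-T, with no gain. The normal density at the 80th percentile is 0.280. Starters' mean = 0.5 × 0.280/0.20 = 0.70; non-starters' mean = -0.5 × 0.280/0.80 = -0.175; *g* = 0.875; bias = -0.175, about -0.17 SD. The correlation between actually starting and HADS-T is then 0.5 × 0.280/√(0.20 × 0.80) = 0.35.
- Both together: *g* = 0.875 - 0.6 = 0.275, bias = -0.20 × 0.275 = -0.055, about -0.05 SD.

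Over *f* = 10% to 30% these three cases run from +0.06 to +0.18, from -0.10 to -0.25, and from about -0.04 to -0.07 SD.

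**4. Error rate and power.** With no true difference as randomised and 50 v 50(1 - *f*) analysed, the noncentrality is *f*|*g*|√(n₁n₂/(n₁ + n₂)). For *f* = 20% and |*g*| = 0.5 it is 0.10 × √(2000/90) = 0.47, and a nominal 5% two-sided test rejects 7.5% of the time. For |*g*| = 1 it rejects 15.4%. These errors mostly favour iCBT when starters end better, and mostly favour TAU when they end worse. Power at 0.6, ignoring bias, falls from 80.4% (45 v 45) to 75.5% (45 v 36, since 45 × 0.8 = 36).

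**The case against.** The strongest reply has four parts.

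- **Asymmetry.** A reader might infer that an iCBT participant who starts other treatment stays in. The article does not say so. It asks participants generally to report changes and is silent on handling in the iCBT arm. What stands is that omission is stated for TAU and no iCBT rule is given.
- **The comparator.** A reader might see a flat contradiction with the TAU section. But GP visits, non-CBT support and continuing medication do not trigger omission, and one section governs access while the other governs data. Both can be followed. They are in tension and the comparator is narrowed; the direct conflict is with intention to treat.
- **Ascertainment.** It is tempting to say that starts are known only if volunteered, and that TAU participants will conceal them. The article asks for reports but does not say that this is the only source. The disincentive is plausible, not documented.
- **Size.** Neither *f* nor *g* is given, and the bias is zero if nobody starts or starters do not differ. If selection and benefit act together, they largely cancel under the assumptions above, leaving about -0.05 SD, which is conservative for iCBT.

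It may also be said that the sentence is only what participants are told, that the rule is disclosed in advance, and that it keeps TAU uncontaminated. The wording is that data will be omitted; if that is not intended, participants are misinformed and the text still needs correcting. Advance disclosure does not restore the randomised comparison. An uncontaminated comparison is a different target from the declared one, and a rule stated for one arm does not deliver it. The article does not say that score collection stops, so an analysis of everyone may remain possible, but it does not commit to one.

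**Conclusion.** The conflict holds as written. A rule that omits randomised TAU participants after a post-randomisation event cannot stand beside a declared intention-to-treat analysis of the primary endpoint, and the planned model does not repair it. The passages must be reconciled.

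The supported conclusion is that the rule can bias the HADS-T contrast, in a direction that the documents do not settle. That it does bias the result, or that it favours iCBT, goes further than the text allows. On an assumed 20% omitted, the illustrative shifts lie between +0.12 and about -0.17 SD for the mechanisms considered, and reach 0.20 SD either way for a 1 SD gap. The power loss is secondary. The bias is the main point, and a larger sample would not remove it.

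Participants' right to ask for their own data to be excluded, in the same consent paragraph, is open to both arms and is a separate matter.

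**What to change.** - Remove the omission rule from the protocol and the participant information. Analyse every randomised participant, with all collected scores, in the allocated arm.
- Record new psychological therapy or psychotropic medication with the same question in both arms at the existing mid- and post-treatment assessments: before lesson 5 and after lesson 8 for iCBT, weeks 8 and 16 for TAU. Report the frequency by arm.
- Confine any exclusion or other handling of such starts to a sensitivity analysis applied in the same way to both arms.

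This changes data handling only, and the sample size need not change. The cost is more than wording. Trial status gives first enrolment as 1 March 2016, so people already told that their data would be omitted may need updated information under an ethics amendment. Those already past an assessment cannot be asked the new question at that time. The contrast may also turn out less favourable to iCBT.
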